**Conclusions:**

This multicenter, randomized, controlled clinical trial will provide evidence on the clinical effectiveness and potential cardioprotective benefits of moxibustion performed at home as a treatment for individuals with phlegm-dampness type of hypertension.

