##### Cardiac-Related Indicators (Measured by 24-Hour Holter Electrocardiogram)

Total heartbeats, myocardial oxygen consumption, average heart rate, heart rate variability (HRV) parameters (ie, percentage of successive NN intervals that differ by more than 50 ms, HRV triangular index, root mean square of successive differences, SD of normal-to-normal [SDNN] intervals, SD of the average normal-to-normal intervals, SDNN index, low-frequency [LF] power, high-frequency [HF] power, and the LF and HF ratio) will be assessed at weeks 0, 4, 12, and 24.

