Potential center effects will be statistically addressed through mixed-effects modeling, notwithstanding standardized central screening and intervention procedures. For primary continuous outcomes, linear mixed-effects models will incorporate the treatment group as a fixed effect and center as a random effect, with center-specific random intercepts accounting for recruitment-related heterogeneity. Secondary outcomes will be analyzed using analogous generalized linear mixed models. The primary analysis will use an intention-to-treat approach. The changes in the primary outcome and other secondary outcomes will be compared by using a linear mixed-effects model with group-by-time point interaction (baseline to week 12). For outcomes measured at multiple time points, a repeated-measures ANOVA will first test for overall group, time, and interaction effects. Upon finding a significant interaction (exact *P* values will be reported), post hoc comparisons will be conducted using a hierarchical adjustment strategy: Benjamini-Hochberg false discovery rate control for the primary outcome across time points and Bonferroni correction for families of secondary outcomes. Sociodemographic and clinical characteristics at baseline will be examined for potential group differences by 2-tailed *t* test or χ^2^ test, with exact *P* values reported. Compliance will be presented using descriptive statistics. The specified significance levels (0.025 for the primary outcome and 0.05 for all other analyses) represent the α thresholds (*P* value cutoffs) for hypothesis testing. All *P* values will be reported per journal style: expressed to two digits (or three if *P*<.01) and as *P*<.001 if below that threshold. Data analysis was conducted with SPSS (version 28.0; IBM Corp).

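### The week-12 comparison of about 34 secondary outcomes is reached by an uncorrected and a Bonferroni-corrected route, and the plan does not say which one decides

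*Protocol article*

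**What the plan says.** All the rules on this point stand in one paragraph of Statistical Analysis.

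- **Route 1, mixed model.** "The changes in the primary outcome and other secondary outcomes will be compared by using a linear mixed-effects model with group-by-time point interaction". The span compared is the 12 weeks of treatment. No multiplicity adjustment is attached to this comparison.
- **Route 2, ANOVA then post hoc.** Outcomes with several time points first go through a repeated-measures ANOVA for group, time and interaction. If the interaction is significant, "post hoc comparisons will be conducted using a hierarchical adjustment strategy". For secondary outcomes that strategy is "Bonferroni correction for families of secondary outcomes". The families are not named.
- **Thresholds.** "The specified significance levels (0.025 for the primary outcome and 0.05 for all other analyses) represent the α thresholds".

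The secondary outcomes are listed under four headings: blood pressure by ABPM, cardiac indicators by Holter, laboratory tests, and scales. The Holter list begins "Total heartbeats, myocardial oxygen consumption, average heart rate, heart rate variability (HRV) parameters" and goes on to nine HRV indices. Only the items under Exploratory Outcomes are labelled exploratory. The abstract concludes that the trial "will provide evidence on the clinical effectiveness and potential cardioprotective benefits of moxibustion performed at home", and the Objective section expects clinical evidence on protection of heart and brain.

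**The concern.** The primary outcome, morning systolic pressure, does not itself measure cardiac or cognitive protection. Any statement about those has to rest on the secondary outcomes, mainly the Holter indices and the Montreal Cognitive Assessment.

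On the literal wording, the Bonferroni correction sits at the end of Route 2. It does not clearly cover the two tests at which a group difference would first appear: the week-12 mixed-model contrast and the ANOVA interaction. An analyst who finds one Holter or metabolic index below 0.05 on Route 1 could report it as a positive result without departing from the plan. An analyst who treats Route 2 as decisive could report the same data as negative. No text makes a claim on a secondary outcome depend on success of the primary.

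The article states that no data analysis has been performed, so the rule can still be settled before results are seen.

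**Working it through.** **Step 1. Count the secondary efficacy outcomes** (sections under Secondary Outcome Measures).

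- ABPM: 8. These are morning diastolic, average systolic and diastolic, night-time systolic and diastolic, circadian rhythm, and systolic and diastolic variability. Repeated labels are counted once, and morning systolic is left out because it is the primary.
- Holter: 12. Three general measures and nine HRV indices.
- Metabolic: 12. Four lipids, fasting glucose, glycated hemoglobin, fasting insulin and five derived indices. Liver and kidney tests are left out because they also serve as safety measures.
- Scales: 2.
- Total: 8 + 12 + 12 + 2 = 34.

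**Step 2. Which outcomes meet which route?** Every secondary outcome is measured at weeks 0, 12 and 24 at least, so all 34 qualify for both routes.

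**Step 3. Uncorrected route if the outcomes were independent.** I take the 0.05 as two-sided and assume no true difference between ST36 and GB39.

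- At least one false positive, either direction: 1 − 0.95^34 = 0.825.
- At least one favouring ST36 (one tail, 0.025): 1 − 0.975^34 = 0.577.

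**Step 4. Uncorrected route with correlation.** The article gives no correlations, so a range is assumed. For m test statistics with common correlation ρ, write each as √ρ·G + √(1−ρ)·e, with G shared and e specific to the outcome. Then

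P(at least one) = 1 − ∫ [Φ((1.96 − √ρ·g)/√(1−ρ)) − Φ((−1.96 − √ρ·g)/√(1−ρ))]^m φ(g) dg.

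For the favourable direction, drop the second Φ term, with every outcome oriented so that positive means benefit. Two structures were used: one correlation across all 34, and correlation only within the four groups, with the groups independent.

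| ρ | All 34: either | All 34: favours ST36 | Within groups: either | Within groups: favours ST36 |
|---|---|---|---|---|
| 0.3 | 0.70 | 0.37 | 0.77 | 0.49 |
| 0.5 | 0.54 | 0.27 | 0.68 | 0.41 |
| 0.7 | 0.35 | 0.18 | 0.56 | 0.32 |

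Over the table, the range is 0.35 to 0.77 in either direction and 0.18 to 0.49 favouring ST36.

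**Step 5. The cardiac, metabolic and cognitive markers alone:** 12 + 12 + 1 = 25. With a common correlation of 0.5, the chance is 0.47 in either direction and 0.23 favouring ST36.

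**Step 6. Bonferroni within the four groups, applied to the week-12 contrast.** Each group is held at or below 0.05. If the groups are independent, the chance of any false positive is at most 1 − 0.95^4 = 0.185. If the groups are dependent, it is at most 4 × 0.05 = 0.20. The outcomes being independent as well gives 0.182, and correlation of 0.3 to 0.7 within groups lowers it to 0.17 to 0.12.

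The article states no family-wise error rate for the secondary outcomes, so there is no figure of its own to reproduce.

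**The case against.** The strongest reply is that the plan does correct across outcomes. It names Bonferroni for families of outcomes, not only of visits, and every secondary outcome passes through the route that ends in that correction. The corrected comparisons can be read as the deciding ones, and then the either-direction risk is about 0.18. This stands as a possible reading. A reader might infer that the correction never reaches week 12, and the text does not support that. But the text does not confirm the corrected reading either, and on both readings the interaction tests are uncorrected.

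A reader might also infer that a chance protective finding is likely, or will occur more often than not. That does not hold. The larger figures count differences in either direction, including against ST36. The favourable chance stays below one half over the assumed correlations and exceeds it only near independence, which is unrealistic for HRV indices from one recording or insulin-resistance indices built from shared inputs. Nor should these rates be set against 0.05 as a multiple: they are family-wise rates, and the plan's 0.05 is a cutoff for each test.

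It is also fair that the abstract speaks only of potential benefits, that one primary outcome is designated, and that unadjusted supportive secondary outcomes are accepted practice. Definition of families is often left to an analysis plan. What remains is that this article does fix a correction, its trigger and its thresholds, and these leave the deciding comparison open.

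**Conclusion.** The concern holds as an unresolved choice between two stated routes. On the uncorrected route, with no true difference, the chance of at least one significant secondary result is about 0.35 to 0.77 in either direction and about 0.18 to 0.49 favouring ST36. With Bonferroni within the four groups, the either-direction chance is at most about 0.19 if the groups are independent.

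These figures rest on the count of 34, a two-sided 0.05, assumed correlations of 0.3 to 0.7 and the article's four headings taken as families. The correlations and the families are my assumptions. The conclusion that the plan permits either route does not depend on them. The point should be settled before analysis because it changes what may be concluded about heart and brain protection.

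**What to change.** Change the Statistical Analysis section in one of two ways.

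1. Apply the Bonferroni correction directly to the week-12 mixed-model contrast, with the four headings under Secondary Outcome Measures as the families, and drop the ANOVA interaction as its trigger.
2. State that all secondary outcomes are supportive, reported as estimates with 95% confidence intervals and with no confirmatory claim. Word the heart and brain statements in the abstract's Conclusions and in the Objective section accordingly.

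Either is a change of wording and needs no further data. The cost is that nominally significant secondary results can no longer be presented as confirmed effects.

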### Dropout Criteria

In this study, the dropout criteria include the following: (1) participants who meet the inclusion criteria but do not complete the trial or who withdraw midway for various reasons; (2) participants who do not follow the prescribed treatment plan or who receive other treatments or medications that interfere with the assessment of efficacy; and (3) participants who are lost to follow-up or die before completing the trial.

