### Statistical Analysis

Data analysis of the primary outcome will be based on the full analysis set constructed by the intention-to-treat principle, whereby patients will remain in their original group regardless of contamination. The per-protocol set will also be analyzed using sensitivity analysis for the primary outcome to evaluate whether contamination affects the direction of the effect. The secondary outcomes will also be compared based on the per-protocol set. The need to impute missing values will be determined by the proportion of and reasons for missing data. If imputation is necessary, appropriate methods, such as the last observation carried forward, the “best-worst-case” scenario, and multiple imputation regression modeling, will be chosen according to the distribution of the missing values.

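### The repeated-measures ANOVA placed ahead of the visit comparisons drops patients with any missed visit unless values are imputed, which for morning systolic pressure does not fit the intention-to-treat set and duplicates the planned mixed model

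*Protocol article*

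**What the plan says.** The Statistical Analysis section names two methods for the same outcomes.

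- **A linear mixed model.** The period it covers ends at week 12: "The changes in the primary outcome and other secondary outcomes will be compared by using a linear mixed-effects model with group-by-time point interaction (baseline to". Center enters as a random intercept.
- **A repeated-measures ANOVA.** "For outcomes measured at multiple time points, a repeated-measures ANOVA will first test for overall group, time, and interaction effects". Post hoc comparisons follow once a significant interaction is found.

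Morning systolic pressure belongs to the second chain as well as the first, because the post hoc rule is "Benjamini-Hochberg false discovery rate control for the primary outcome across time points and Bonferroni correction for families of secondary outcomes".

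The analysis set for the primary outcome is explicit: "Data analysis of the primary outcome will be based on the full analysis set constructed by the intention-to-treat principle". For the secondary outcomes the wording differs: "The secondary outcomes will also be compared based on the per-protocol set".

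On missing data: "The need to impute missing values will be determined by the proportion of and reasons for missing data". If imputation is judged necessary, the candidates are methods "such as the last observation carried forward, the “best-worst-case” scenario, and multiple imputation regression modeling". The Dropout Criteria anticipate incomplete patients, among them "participants who meet the inclusion criteria but do not complete the trial or who withdraw midway for various reasons", but no dropout rate is given.

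The visit schedule (Table 1; Assessment and Outcomes) puts ambulatory pressure and Holter monitoring at weeks 0, 4, 12 and 24. The scales and most laboratory tests are at weeks 0, 12 and 24. The primary outcome is defined on weeks 0 and 12, but morning systolic pressure appears again among the secondary measures at all four visits. The software is SPSS 28.

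**The concern.** A classical repeated-measures ANOVA, including the standard SPSS procedure, needs a complete row for each patient. A patient missing one scheduled visit is removed from the group, time and interaction tests altogether. For morning systolic pressure over four visits, a patient measured at weeks 0, 4 and 12 who misses week 24 contributes nothing, although the value that defines the primary outcome was observed.

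For the primary outcome this step would therefore describe patients who attended every visit, while the article promises an intention-to-treat full analysis set. The mixed model in the same paragraph keeps incomplete patients. The two methods can thus rest on different patients and disagree, and the ANOVA, which comes first, decides whether the visit comparisons are opened. At stake are observed data thrown away, a possible selection effect among completers, and two answers to one question.

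**Working it through.** **1. No planned figure to reproduce.** The article gives no dropout rate, missingness pattern or between-visit correlation, so everything below is a range on stated assumptions. Taken from the article: 120 patients allocated 1:1, an expected difference of 7.2 mm Hg and an SD of 3.3 mm Hg (Abstract; Sample Size Calculation).

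**2. Patients deleted.** Assume each of the three post-baseline ambulatory visits is missed independently with probability m, baseline is complete and nothing is imputed. The share deleted is 1 − (1 − m)³, and the share lacking week 12 is m.

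| m | Deleted | Left of 120 | Lacking week 12 | Deleted despite a week-12 value |
|---|---|---|---|---|
| 5% | 1 − 0.95³ = 14.3% | 102.9 | 5% | 14.3 − 5 = 9.3% |
| 7% | 1 − 0.93³ = 19.6% | 96.5 | 7% | 19.6 − 7 = 12.6% |

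Outcomes with two post-baseline visits lose less: 1 − 0.95² = 9.8% and 1 − 0.93² = 13.5%.

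**3. Direction of any bias.** A simulation used 60 patients per arm, SD 3.3 and a true week-12 difference of 7.2. Assumed: differences of 5 at weeks 4 and 24, between-visit correlations of 0.4 to 0.8, and 10% or 20% of all patients incomplete. The week-12 difference among completers (mm Hg) was:

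| Who is incomplete | 10% | 20% |
|---|---|---|
| Low week-4 responders in either arm, one common threshold | 6.4–6.8 | 5.8–6.5 |
| Low week-4 responders, treatment arm only | 7.7–8.1 | 8.1–8.9 |
| Low week-4 responders relative to their own arm (equal relative dropout) | 7.2 | 7.2 |
| Low week-12 responders who then miss only week 24 | 6.1 | 5.2 |

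A likelihood estimate using all observed values returned 7.2 in every row. That is expected, because in each scenario missingness depends only on values already observed. It shows what the mixed model gains when that condition holds, not that it always holds.

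**4. Would the ANOVA's conclusion change?** It tests for zero effects. Take a separate simulation in which the full 7.2 is already present at week 4, the correlation is 0.7, and 20% leave on a common threshold. Completers differ by 5.79, with about 1% dropout under treatment and 39% under control, leaving about 59 and 37 patients. The standard error is 3.3 × √(1/59 + 1/37) = 0.69, and 5.79 / 0.69 ≈ 8.4. On the article's own effect size, a test against zero is not in danger.

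**The case against.** The strongest reply has four parts.

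- **Nothing restricts the ANOVA to completers.** Correct. Deletion follows from how the method works on incomplete rows, and it does not occur if values are imputed. But imputation is conditional, and two of the listed options, carrying the last value forward and best-worst-case, make the result depend on a later choice. The mixed model under missingness at random needs no such choice.
- **The treatment comparison is the mixed model.** Largely right. A reader might infer that the primary analysis is itself a completers analysis. The article does not support that, since changes to week 12 are compared with a mixed model under intention to treat. What remains is that the overall tests and the route to the across-visit comparisons run through the ANOVA.
- **The bias is assumed.** Also right. A reader might infer that completers necessarily understate the effect because poor responders leave the control arm. The article gives no basis for that pattern, and the simulation shows shrinkage, inflation or no bias depending on who leaves. Nor can the shrinkage be set against the 5 mm Hg superiority margin, because the ANOVA does not test against that margin.
- **The scope is narrower than every outcome.** Right. Scales and most laboratory tests have three visits. The full-analysis-set sentence covers only the primary outcome, and the per-protocol set is named for the secondary outcomes.

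When and how to impute may well be settled in an analysis plan that is not shown. The naming of two methods that treat incomplete patients differently is in the article itself.

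**Conclusion.** The point holds in a limited form. For morning systolic pressure, a first-step repeated-measures ANOVA without imputation would discard patients whose week-12 value is known. That does not fit the stated full analysis set and duplicates a planned model that keeps those patients. With 5–7% missing independently per post-baseline visit, 14–20% of patients would be deleted. These rates are assumptions.

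Bias among completers is possible but not established: 5.2 to 8.9 mm Hg against a true 7.2 across the scenarios tried, and nil when relative dropout is equal. No scenario here shows the ANOVA's conclusion for the primary outcome reversing. This is an inexpensive improvement to a stated method, not evidence that the primary comparison is invalid.

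**What to change.** Delete the repeated-measures ANOVA. Take the overall group, time and interaction tests and the visit contrasts from one linear mixed model using all available observations, on the full analysis set for the primary outcome. The model should have:

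- visit as a categorical factor, with each outcome's own scheduled visits;
- group and group-by-visit terms;
- an unstructured within-patient covariance;
- the center random intercept already planned.

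The week-12 contrast stays the primary comparison. Whether a significant interaction should be required before the visit contrasts, and how those contrasts are adjusted, are separate questions that this change does not settle.

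The cost is a wording change: a mixed model is already planned, and SPSS can fit it. The Results section says that no data analysis has been performed, so the change can be recorded before analysis. The small downside is reliance on a missing-at-random assumption, which is weaker than what a completers ANOVA generally needs.

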### Assessment and Outcomes

#### Overview

Participants will undergo evaluations at weeks 0, 2, 4, 6, 8, 10, 12, and 24 during outpatient visits. Twenty-four-hour ambulatory blood pressure and 24-hour Holter electrocardiogram will be examined at weeks 0, 4, 12, and 24. General information (weight, height, waist circumference, hip circumference, family history, medical history, concomitant medications, and lifestyle behavior), relevant laboratory tests (4 items of lipids, fasting blood glucose, glycosylated hemoglobin, serum insulin, homeostatic model assessment of insulin resistance, homeostatic model assessment of β-cell function, insulin-sensitivity index, triglyceride-glucose index, metabolic score for insulin resistance, liver function, and kidney function), heart function, vascular risk stratification, and scale assessment (TCM phlegm-dampness physique score and the Montreal Cognitive Assessment) will be examined at weeks 0, 12, and 24. Major unconscionable cerebrovascular injury, target organ injury, and moxibustion adverse events will be recorded during the study period.

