#### Primary Outcome Measure

In this study, the primary outcome measure is the morning systolic blood pressure, which will be measured by 24-hour ABPM (assessment at weeks 0 and 12).

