#### Secondary Outcome Measures

##### Blood Pressure–Related Indicators (Measured by 24-Hour ABPM)

Morning diastolic blood pressure, average systolic blood pressure, average diastolic blood pressure, nighttime systolic blood pressure, nighttime diastolic blood pressure, and circadian rhythm of blood pressure will be assessed (at weeks 0, 4, 12, and 24). Twenty-four-hour diastolic blood pressure, 24-hour nocturnal systolic blood pressure, 24-hour nocturnal diastolic blood pressure, 24-hour morning systolic blood pressure, 24-hour morning diastolic blood pressure, circadian rhythm of blood pressure, 24-hour systolic blood pressure variability, and 24-hour diastolic blood pressure variability will also be assessed at different time points (at weeks 0, 4, 12, and 24)

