##### Laboratory Tests

Triglycerides, cholesterol, high-density lipoprotein, low-density lipoprotein, fasting blood glucose, glycated hemoglobin, fasting insulin, homeostatic model assessment of insulin resistance, homeostatic model assessment of β-cell function, insulin-sensitivity index, triglyceride-glucose index, metabolic score for insulin resistance, and liver and kidney function will be measured at weeks 0, 12, and 24.

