##### Scale Evaluations

The TCM phlegm-dampness constitution score, Montreal Cognitive Assessment will be administered at weeks 0, 12, and 24.

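### If week 0 counts as a time level, the repeated-measures ANOVA's overall group test averages in a pre-treatment visit and does not estimate the effect of ST36 versus GB39

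*Protocol article*

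**What the plan says.** The Statistical Analysis section of the protocol article describes two analyses of the repeated outcomes.

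- A mixed model for change: changes in the primary and secondary outcomes "will be compared by using a linear mixed-effects model with group-by-time point interaction (baseline to week 12").
- A repeated-measures ANOVA: "For outcomes measured at multiple time points, a repeated-measures ANOVA will first test for overall group, time, and interaction effects". The next step hangs on one of its three tests: "Upon finding a significant interaction (exact *P* values will be reported), post hoc comparisons will be conducted using a hierarchical adjustment strategy".

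The outcome sections give the visits. In the Overview, "Twenty-four-hour ambulatory blood pressure and 24-hour Holter electrocardiogram will be examined at weeks 0, 4, 12, and 24". For laboratory tests, "liver and kidney function will be measured at weeks 0, 12, and 24", and for the scales, "Montreal Cognitive Assessment will be administered at weeks 0, 12, and 24". (Table 1 also ticks lipids at week 4, which would put them with the four-visit outcomes.) Every schedule begins at week 0. The ANOVA sentence does not say whether week 0 is a response level or is handled in some other way, and the section does not mention baseline as a covariate.

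**The concern.** In a repeated-measures ANOVA the group main effect is the arm difference averaged over all levels of time. Week 0 is measured before any moxibustion, so randomization makes its expected arm difference zero. With week 0 as a level, the main effect is pulled toward zero by a known fraction, and any chance difference at week 0 feeds into it. It then estimates neither the change to week 12 nor the mean effect after treatment starts.

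The plan names this effect as one to be tested and does not say how it is to be read. A reader of the results may take its P value as the test of treatment. This matters most for weeks 4 and 24. The mixed model is stated for baseline to week 12, so week 24 lies outside it and week 4 is not named in it. For those visits the ANOVA is the only test explicitly described.

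**Working it through.** The documents give no figure for this test, so there is none to reproduce.

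**Inputs.** From the article: 120 patients allocated 1:1, so n = 60 per arm, and m = 4 visits (weeks 0, 4, 12, 24) or m = 3 (weeks 0, 12, 24). Assumed: single-visit SD of 1, compound symmetry with between-visit correlation ρ = 0.6 (range 0.4 to 0.7), an effect d = 0.5 SD that is constant after week 0, two-sided α = 0.05, no dropout. Let k = m − 1 be the number of post-baseline visits.

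**1. Share of the effect kept.** The main effect is (0 + k·d)/m = d·k/m.
- Four visits: 3/4.
- Three visits: 2/3.

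**2. Baseline imbalance carried in.** With no treatment effect and a chance week 0 difference B, the expected main effect is B·(1 + kρ)/m.
- Four visits: 2.8/4 = 70% of B.
- Three visits: 2.2/3 = 73% of B.

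**3. Power of the group test.** SE = √[(2/n)(1 + kρ)/m].
- Four visits: 0.375 / √(0.03333 × 0.700) = 0.375/0.1528, z = 2.455, power 69%.
- Three visits: 0.3333 / √(0.03333 × 0.7333) = 0.3333/0.1563, z = 2.13, power 57%.

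**4. Power of the interaction test.** Noncentrality = (n/2)·d²·(k/m)/(1 − ρ).
- Four visits: 30 × 0.1875/0.4 = 14.06 on 3 and 354 df, power 89%.
- Three visits: 30 × 0.1667/0.4 = 12.5 on 2 and 236 df, power 89%.

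**5. Power of the comparison of change to week 12.** SE = √[(2/n)·2(1 − ρ)] = √(0.03333 × 0.8) = 0.1633. The ratio is 0.5/0.1633 = 3.06, noncentrality 9.375 on 1 and 118 df, power 86%.

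**6. Power of the baseline-adjusted mean of post-baseline visits.** SE = √[(2/n)((1 + (k − 1)ρ)/k − ρ²)].
- Four visits: √(0.03333 × 0.3733) = 0.1116, z = 4.48, power 99%.
- Three visits: √(0.03333 × 0.44) = 0.1211, z = 4.13, power 98%.

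Part of that gain comes from averaging visits. For week 12 alone with baseline as covariate, SE = √[(2/n)(1 − ρ²)] = √(0.03333 × 0.64) = 0.1461, z = 3.42, power 93%, against 86% in step 5.

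**7. Sensitivity to the assumed correlation, ρ from 0.4 to 0.7.**

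| Test | Power |
|---|---|
| Group effect, four visits | 65–79% |
| Group effect, three visits | 53–65% |
| Interaction | 73–96% |
| Change to week 12 | 70–94% |
| Baseline-adjusted post-baseline mean | at least 96% |

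The group test loses power as ρ rises; the others gain.

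**8. Smaller effect.** For d = 0.3, four visits and ρ = 0.6, the same formulas give 31% (group), 44% (interaction) and 77% (baseline-adjusted mean).

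**The case against.** The strongest reply is that the plan rests no decision on the group effect. The only trigger for further comparisons is the interaction, and with week 0 as a level the interaction tests whether the arms change differently, without dilution. Changes to week 12, for secondary outcomes as well as the primary, go to a group-by-time mixed model, which is also undiluted. This stands, and it confines the point to a secondary P value and to efficiency.

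The reply may add that week 0 is not stated to be a level, and that an ANOVA on changes or on post-baseline values is not excluded. That also stands, so the dilution is conditional. Inclusion is still the natural reading, since every schedule starts at week 0 and the mixed model runs from baseline.

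Three stronger readings are tempting, and the documents do not support them.

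- A reader might infer that the primary result could slip below the 5 mm Hg superiority margin. Nothing in the article sets an average over visits against that margin; the primary outcome is the change to week 12.
- A reader might put the dilution at a half. With a constant effect, that needs only two visits, weeks 0 and 12. This is the primary outcome's schedule, and there the planned comparison of change is undiluted. With more visits it needs an uneven effect over time, and the article gives no such pattern.
- A reader might say that a non-significant interaction leaves the group test as the only between-arm P value. The interaction is itself a between-arm P value.

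**Conclusion.** The point holds as a conditional and limited one. If week 0 is a level of time, the overall group effect keeps 3/4 or 2/3 of a constant effect, carries about 70% of any chance baseline difference (at ρ = 0.6), and is not an estimate of ST36 versus GB39. The article does not say that this test carries no efficacy conclusion.

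The planned efficacy inference is not corrupted. In the 0.5 SD scenario with four visits, the tests the plan acts on have 89% and 86% power, against 69% for the group effect, and a baseline-adjusted mean would reach 99%. The retained fractions assume equal visit weights and a constant effect after week 0. The power figures also assume compound symmetry, full follow-up and a correlation that the article does not give. If the effect fades after treatment ends at week 12, the advantage of averaging over post-baseline visits shrinks, which is why week 12 should be reported first. The change is worth making because it is free and improves on both ANOVA tests.

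**What to change.** In the Statistical Analysis section, or in the SAP if it governs, replace the ANOVA sentence with one stating that:

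- post-baseline visits are the repeated outcomes and week 0 is a covariate, with the planned center random intercept kept;
- the arm difference is reported at each post-baseline visit, week 12 first;
- any single overall figure is the baseline-adjusted mean over post-baseline visits.

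If the ANOVA is kept, the minimum is to say whether week 0 is a level of time and that the group main effect then carries no efficacy conclusion.

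The cost is one sentence. Week 0 is already in the visit schedule, so no new data are needed, and the Results section says that no analysis has yet been performed.
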